To increase the willingness of individuals with obesity to undergo weight loss, we must educate them on their condition and reasons to lose weight. Weighing is key to this; however, in our study, 53.3% of merchant women with obesity did not weigh themselves once a year, and 95.5% of them did not own a scale. Regular weighing is effective for weight loss even without interventions such as weight loss programs [11] and is one of the most cost-effective and easiest weight loss methods to implement. In this study, we aim to increase the awareness of one’s own weight through regular weighing, promote awareness of health risks, and increase readiness for weight loss.

Noninvasive exercise and diet are the cornerstones of behavioral therapy as a treatment method for obesity [12]; overweight and obesity management guidelines [13] that include behavior change programs have been established in the United States. However, these are primarily conducted by primary care physicians in medical institutions and require advanced medical personnel and resources such as frequent counseling and elaborate individualized behavioral strategy planning. Therefore, implementing these behavior change programs as is in resource-limited countries such as Côte d'Ivoire is challenging [14,15].

Mobile health is cost-effective and impactful in supporting diet and exercise regimens [16-20]. Self-monitoring using smartphones is more effective than other methods of weight management [20]. Enhanced social support through online social networking services (SNSs) can also be effective. For example, Facebook groups have shown weight loss benefits [21]. In Côte d'Ivoire, WhatsApp is a popular private communication tool; however, studies on implementing behavior change using WhatsApp are limited [22]. Most studies that use smartphone apps and SNSs have been conducted in high-income countries. Such studies are limited in sub-Saharan Africa because sociocultural backgrounds and the use of smartphones and SNSs are different.

The prevalence of smartphones in sub-Saharan Africa was 45% in 2019 and is expected to steadily increase [23]. In our previous study, 77% of female traders in the target markets used smartphones [8], suggesting that interventions using smartphones are feasible. Smartphone use is important in areas requiring low-cost interventions.

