Health education should include recommendations for and emphasize the importance of a healthy diet, exercise, and weight measurement. Diet and exercise content should be in line with the “Diet and Exercise” described in the “Obesity” chapter of the Côte d'Ivoire National Disease-Specific Cookbook Guidelines [33]. In-person or telephonic health education will be conducted once a month and tailored to the stages of behavioral change [26] (precontemplation, contemplation, preparation, action, and maintenance) of the target population. Interventions corresponding to the change process [34-36] of each stage are provided. The intervention stimulates interest in weight loss during the precontemplation stage, motivates implementation during the contemplation stage, supports implementation during the preparation stage, supports continuation during the action stage, and supports maintenance during the maintenance stage to maintain confidence in behavior. The intervention and evaluation schedules are shown in Table 2.

To maintain consistency among supporters in the intervention, a manual was developed on how to send health education material via WhatsApp. A manual for telephone interviews was developed, and supporters will conduct telephone interviews according to the manual and provide a report on the content of the interviews. Supporters will be trained on the content of the intervention and the survey to ensure the quality of the intervention and the survey.

No interventions are administered in the control group. For the control group, height and weight are measured at baseline and at data collection at 3, 6, and 12 months, and BMI is calculated and reported on the spot by the supporter. This allows participants in the control group to know their weight and BMI regularly. In addition, after the 12-month survey is completed, scales will be installed in the target markets free of charge so that participants can continue to measure their weights. In addition, we will introduce the app to those who wish to use it.

**Table 1 table1:** Adaptations of the weight loss program following the American Heart Association (AHA)/American College of Cardiology (ACC)/The Obesity Society (TOS) guidelines for the management of overweight and obesity in adults.

Variable	AHA/ACC/TOS guidelines [13]	Intervention adapted to this study	Reason for adaptation

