### Outcome

The primary end point of the study is to compare weight changes from baseline to the end of the intervention (6 months later) between the intervention and control groups.

Secondary end points include the differences in body fat percentage, abdominal circumference, stage of behavioral change in weight loss behaviors such as diet and exercise, percentage of individuals with correct weight perception, degree of body pain (with visual analog scale [VAS]), and self-rated health at the end of the intervention (6 months later) compared to baseline. Simultaneously, the intervention group will be evaluated in terms of the frequency of inputs to the self-monitoring apps, degree of participation in WhatsApp groups, average number of steps taken, and degree of weight loss during the intervention period.

To evaluate the interim process of the intervention, the intervention and control groups will be compared and analyzed in the same manner as described above, 3 months after the start of the intervention. In addition, the intervention group will be evaluated for weight change at 1, 2, 4, and 5 months and for changes in the behavioral change stage of weight loss behaviors such as diet and exercise.

As a follow-up evaluation after the intervention, both groups will be evaluated at 12 months (6 months after the end of the intervention) in the same way.

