### Statistical Methods

The primary outcome will be evaluated by comparing the difference in weight change between the intervention and control groups 6 months after the intervention ended. In addition, the effectiveness of the weight loss intervention will be estimated using a linear regression model with weight change at 6 months as the dependent variable and the affiliation group, stratification variables, and other sociodemographic attributes as covariates.

Among the secondary outcomes, weight, body fat percentage, abdominal circumference, and degree of body pain (VAS scale) will be measured and compared in the same way as the primary outcome at all evaluation periods (3, 6, and 12 months). Other secondary outcomes will be compared to differences in rates at baseline and 3, 6, and 12 months. These analyses will follow the intention-to-treat principles. Additionally, intention-to-treat and per-protocol analyses will be performed and compared to address cases of protocol noncompliance.

Within the intervention groups, weight loss will be used as the dependent variable, and linear regression model analyses will be performed to estimate the impact of self-monitoring input frequency, WhatsApp group participation, and sociodemographic characteristics as covariates.

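### Stage of change, a five-level ordered secondary outcome, is compared only as rates, which ignores the ordering and does not use each woman's own baseline stage

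*Protocol article*

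**What the plan says.** The Outcome section of the protocol article lists six secondary end points. They include "stage of behavioral change in weight loss behaviors such as diet and exercise, percentage of individuals with correct weight perception". The list closes with "self-rated health at the end of the intervention (6 months later) compared to baseline". The Intervention section gives the stages in order: "precontemplation, contemplation, preparation, action, and maintenance".

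Statistical Methods divides the secondary outcomes in two. The first group, which gets the method used for weight change at 6 months, is named: "Among the secondary outcomes, weight, body fat percentage, abdominal circumference, and degree of body pain (VAS scale) will be measured and compared in the same". The rest get one sentence: "Other secondary outcomes will be compared to differences in rates at baseline and 3, 6, and 12 months". Stage of change is not in the first group, so it is analysed by rates. No ordinal method is named for it, and no model that includes a woman's own baseline stage.

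In the Background section, the authors say they want regular weighing to "promote awareness of health risks, and increase readiness for weight loss". The study aim at the end of the Introduction and the Hypothesis section are about weight loss.

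**The concern.** A rate can represent a five-level ordered variable in two ways. The stages can be cut into two groups, at one of four possible points, or the share in each stage can be compared without regard to order. A cut removes all movement on the same side of it. With a cut at action, for example, a woman who goes from precontemplation to preparation counts as unchanged; with a cut at preparation she counts as changed. An unordered comparison spreads the test over four degrees of freedom, although the effect expected is a shift in one direction.

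Baseline stage is measured in every woman and is likely to predict later stage. A comparison of rates uses it at most through the group's baseline rate.

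What is at stake is the precision of the one secondary outcome that shows whether readiness moved. A real shift could be reported as inconclusive. The test of weight change does not depend on it.

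**Working it through.** **1. The plan's own sample size (Sample Size Calculation section).** Inputs: difference 1.5 kg, SD 3.7 kg, z-values 1.96 and 0.842, dropout 10%.

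n per arm = 2 × (1.96 + 0.842)² × 3.7² / 1.5² = 95.5, rounded up to 96. Then 96 / 0.9 = 106.7, rounded up to 107, against 108 stated. This agrees within rounding. With 108 × 0.9 = 97 evaluable per arm, power for weight is 80.6%. No power is stated for stage of change.

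**2. Assumptions for stage of change.** 97 evaluable per arm, two-sided 5%, common odds ratio 2.0. On the latent logistic scale this is ln 2 / 1.814 = 0.38 SD, close to the weight effect of 1.5 / 3.7 = 0.41 SD. Four control-arm stage distributions were tried. The one with 40% in precontemplation is anchored on the 40.1% in Background who did not wish to lose weight; equating the two is an assumption.

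**3. Formulae.** Ordinal test (Whitehead): V = (N/12)(1 − Σp̄³), where p̄ is the mean of the two arms' stage probabilities; power = Φ(ln OR × √V − 1.96). Single rate: two-proportion normal approximation at each cut. Five unordered rates: noncentral chi-square, 4 df.

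Worked case, equal fifths:
- With odds ratio 2.0 the intervention-arm probabilities are 0.111, 0.139, 0.179, 0.238, 0.333. Σp̄³ = 0.0449 and V = (194/12) × 0.9551 = 15.44. Power = Φ(0.693 × 3.93 − 1.96) = Φ(0.76) = 78%.
- Action or later: 40.0% v 57.1%, power = Φ((0.1714 − 1.96 × 0.0718) / 0.0707) = Φ(0.435) = 67%.
- Contemplation or later: 80.0% v 88.9%, power 40%.

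**4. Power (%) at odds ratio 2.0, without baseline stage.**

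| Control-arm stages (%) | Ordinal | Contemplation+ | Preparation+ | Action+ | Maintenance | Five unordered rates |
|---|---|---|---|---|---|---|
| 20/20/20/20/20 | 77.7 | 40.0 | 60.8 | 66.8 | 55.6 | 55.4 |
| 40/25/15/12/8 | 77.2 | 60.8 | 66.0 | 55.6 | 31.9 | 54.7 |
| 20/30/25/15/10 | 77.6 | 40.0 | 65.5 | 60.8 | 37.3 | 55.1 |
| 60/20/10/6/4 | 72.9 | 66.8 | 55.6 | 37.3 | 19.3 | 50.1 |

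Against the ordinal test, the loss is 6–17 points at the best or second-best cut, 38–54 at the worst, and 22–23 for unordered rates.

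**5. Other effect sizes, same four distributions.** At odds ratio 1.5 the ordinal test has 32–36% and the best cut 28–29%. At 2.5 they have 93–95% and 87–89%.

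**6. Baseline stage (simulation, odds ratio 2.0, first two distributions).** The ordinal model with baseline stage as a covariate had 79–82%, 83–84% and 92–93% power at latent baseline-to-follow-up correlations of 0.3, 0.5 and 0.7 (400 runs each, Monte Carlo standard error about 2 points). If the plan means change in rate from baseline, at preparation or later or at action or later, power was 41–48%, 47–56% and 56–67% at the same correlations (4,000 runs each). That is no better than the follow-up rate alone, and clearly worse at 0.3 and 0.5.

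**The case against.** Much of the case on the other side stands, and it limits the point.

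- *Baseline.* A reader might infer that baseline is thrown away. The documents do not support this: Statistical Methods names rates at baseline, and Outcome defines these end points relative to baseline. What is absent is each woman's own stage as a covariate. The wording leaves open whether change in rates or rates at each visit is meant.
- *Aim.* A reader might take raised readiness as the trial's main aim. The stated aim and hypothesis are weight loss in a community that includes women with little readiness. Raising readiness is a step towards that. Stage of change is secondary and did not drive the sample size.
- *Cut-point.* It is tempting to call the missing cut-point an error in an unblinded trial. A condensed article may leave it to an analysis plan that is not shown, so it is not an error in itself. The article also never says that the stages will be cut at action.
- *Choice of model.* The intervention differs by stage, so one common odds ratio is not self-evident, and a rate at a threshold fixed in advance is easy to interpret.
- *Diet and exercise separately.* Data Collection Methods specifies diet and exercise stages only for the intervention group's monthly calls. For both arms it mentions stages related to weight loss, and the survey form is not shown.

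None of this defends rates as the only comparison of an ordered outcome. The method is stated, not left open.

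**Conclusion.** The point holds in limited form. The only between-group analysis that the article states for stage of change ignores the order of its five levels and does not use each woman's baseline stage. This concerns one secondary outcome and leaves the primary analysis untouched.

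The ordinal test had more power than any form of rate in every scenario tried, but the size of the gain is not known. It depends on the assumed odds ratio, stage distribution, cut-point and baseline correlation, and the calculation itself assumes proportional odds, which favours the ordinal model. A blanket statement that most of the power is lost would not be supported: the loss is modest with a well-placed cut and large with a poor one or with unordered shares. The further gain from baseline stage is small at correlation 0.3 and about 15–20 points at 0.7.

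The same sentence in Statistical Methods also covers self-rated health. The article does not give its scale, so no claim is made about it here.

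**What to change.** Replace the comparison of rates for stage of change as follows:

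- At 3, 6 and 12 months, analyse stage as recorded in both arms with a proportional-odds model on arm, baseline stage and the BMI and age strata. Report the common odds ratio with its 95% CI.
- Model diet and exercise separately only if the survey form records them separately in both arms.
- Show the percentage in each stage, by arm and visit, as description.
- Fix in advance any cut-point that is kept.
- For correct weight perception, keep the binary comparison but adjust it for the baseline value.

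This changes analysis wording only. Table 2 schedules the structured interview, which includes stage of change, at baseline, 3, 6 and 12 months in both arms. The Results section reports the baseline survey as still under way at the end of November 2024, so the change could be made before follow-up data existed. The small downside is the proportional-odds assumption, which the category percentages let readers check.

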### Data Collection Methods

Data will be obtained from supporters visiting the market to conduct face-to-face structured interviews (Multimedia Appendix 1) and anthropometric measurements. Body measurements will be taken at the time of recruitment to measure height and weight, and BMI will be calculated immediately. Subsequent data collection will include weight measurements, body fat percentage, and abdominal circumference. Height will be measured using a hardware SHUREMAN Lock Convex measuring tape (Kenoh Co, Ltd, Japan, model LC-5525) with a locking function, and an InBody (InBody Japan Inc, model H20N) will be used as the body composition scale. Structured interviews will be conducted using a questionnaire asking about sociodemographics, weight perception, behavioral change stages related to weight loss, behaviors related to weight management, body pain level (using the VAS scale), and the use of smartphone apps for weight management.

In addition, the intervention group will be asked about the weight and behavioral change stages of exercise and diet during the monthly telephone intervention.

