### Comparisons With Prior Work

There are fewer community-based weight loss programs in sub-Saharan Africa than those conducted within health care facilities. One such program is that of Herrmann et al [25]; however, it primarily involves interventions led by health care professionals with specialized knowledge and does not use smartphones or web-based media.

In our study, we deliberately chose to use nonmedical staff as direct interventionists to evaluate the feasibility of implementing a weight loss program by those staff in sub-Saharan African countries where human resources in health care are particularly scarce.

Additionally, weight loss programs that use smartphone apps often recruit participants via web-based media, thereby primarily attracting individuals who are already motivated to lose weight [20]. Our study differs from previous research in that it targets communities with cultural norms that view being plump as a virtue, includes individuals who may not be aware of the need to lose weight, and recruits participants through face-to-face interactions.

To our knowledge, this is the first study to implement a smartphone app–based weight loss program in sub-Saharan Africa that does not require direct intervention by health care professionals and targets specific communities.

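### The within-arm regression sets out to estimate the impact of app logging and WhatsApp participation, but as written it cannot separate an effect from readiness to lose weight or from reverse causation

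*Protocol article*

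**What the plan says.** The protocol article, Statistical Methods, describes this analysis in one sentence: "Within the intervention groups, weight loss will be used as the dependent variable, and linear regression model analyses will be performed", the purpose being to "estimate the impact of self-monitoring input frequency, WhatsApp group participation, and sociodemographic characteristics as covariates". Apart from the two engagement measures, sociodemographic characteristics are the only terms named.

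That sentence gives no time window. The Outcome section supplies one. It says that "the intervention group will be evaluated in terms of the frequency of inputs to the self-monitoring apps, degree of participation in WhatsApp groups", and the same list goes on to "average number of steps taken, and degree of weight loss during the intervention period". Engagement and weight loss are therefore both evaluated over the intervention period.

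Data Collection Methods shows what else will be on file. The structured interview covers "weight perception, behavioral change stages related to weight loss, behaviors related to weight management". Table 2 schedules that interview and a weight measurement at month 0 and at months 3, 6 and 12. The article does not describe this regression as associational or exploratory.

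**The concern.** Randomisation protects the comparison between arms. It does not protect a comparison of frequent and infrequent loggers inside one arm, because the women set their own level of engagement after allocation. Two other explanations then compete with a real effect.

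- **Readiness.** A woman who wants to lose weight may both log more and lose more. The trial expects a wide range of readiness: Comparisons With Prior Work notes that the study "includes individuals who may not be aware of the need to lose weight", and the Background reports that 40.1% of merchant women with obesity in the target market did not wish to lose weight. The monthly education is also tailored to stage of change, so stage may influence the support received. Stage is measured but not named in this model.
- **Reverse causation.** Exposure and outcome cover the same months. Losing weight can encourage further logging, and failing to lose can end it. Nothing in the model puts engagement before the weight change.

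At stake is how a positive coefficient is read. If it is reported as an impact, it could be taken as evidence that logging or messaging causes weight loss, which this analysis cannot show.

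**Working it through.** **The plan's own figure.** The article gives no figure for this regression. Its only related figure is the sample size for the primary comparison. With a difference of 1.5 kg, SD 3.7 kg, two-sided 5% and 80% power:

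n per arm = 2 × (3.7 × (1.96 + 0.842) / 1.5)² = 95.5, so 96.

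The usual small-sample t adjustment adds about 1, giving 97, and 97 / 0.9 rounds up to 108. The stated 108 per group is reproduced. With 10% dropout, 108 × 0.9 = 97.2, so about 97 women enter the within-arm model.

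**Readiness as confounder.** Suppose logging has no effect, and motivation correlates *a* with logging and *a* with weight loss. These correlations are assumptions; the article gives none.

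- Spurious correlation: r = a × a.
- Test statistic centre: z = atanh(r) × √(97 − 3).
- Rejection probability: P(|Z| > 1.96) with Z centred at z.
- Spurious slope per SD of logging: r × 3.7 kg.

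| a | r | z | Rejection, formula | Rejection, simulation | Spurious slope (kg per SD) |
|---|---|---|---|---|---|
| 0.1 | 0.01 | 0.10 | 5% | 5% | 0.04 |
| 0.2 | 0.04 | 0.39 | 7% | 6% | 0.15 |
| 0.3 | 0.09 | 0.87 | 14% | 15% | 0.33 |
| 0.4 | 0.16 | 1.56 | 35% | 36% | 0.59 |
| 0.5 | 0.25 | 2.48 | 70% | 69% | 0.93 |

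The simulation used 97 women, SD 3.7 kg and 4,000 runs per row, and fitted a linear model with logging and one sociodemographic variable. That variable was generated independently of motivation, so adjusting for it removed none of the bias. A sociodemographic variable related to readiness would remove some.

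**Reverse causation.** Again with no effect of logging, total loss was split into two independent halves of equal variance (early and late), and logging was correlated *g* with the early half. The expected spurious slope is g × 3.7 / √2.

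| g | Slope, formula (kg per SD) | Slope, simulation | Rejection, simulation |
|---|---|---|---|
| 0.1 | 0.26 | 0.27 | 11% |
| 0.2 | 0.52 | 0.53 | 29% |
| 0.3 | 0.78 | 0.77 | 54% |
| 0.4 | 1.05 | 1.05 | 81% |

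For scale, the trial is sized on a between-group difference of 1.5 kg.

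**The case against.** **The covariate list may be left to the analysis plan.** The article gives this model one sentence, does not say that sociodemographics are the only adjustment, and condenses a fuller document. That has weight: a fuller plan may name more terms, and silence on covariates alone would not be a finding. What stands is that the article does state an aim, to estimate an impact, and no covariate list makes that aim attainable for self-selected engagement measured alongside the outcome.

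**The word may be loose.** The same sentence speaks of the impact of sociodemographic characteristics, which suggests that predictors of weight loss are meant. If so, saying *association* costs nothing.

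**The time window is inferred.** The regression sentence gives none. This is correct; the shared period comes from the Outcome section and is a reasonable reading, not an explicit model specification.

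**The size is assumed.** This is also correct. For confounding at correlations of 0.1 to 0.2 the error rate is close to nominal, and at 0.4 about 65% of such analyses would still be non-significant. A reader might infer that a spurious effect will appear. The figures support only that one can appear. They also treat logging alone, whereas the planned model has a second engagement term and further covariates.

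**The policy harm is not in the documents.** A reader might infer that this regression would be used to choose components or to justify policy use of the app. The Conclusions and Study Significance and Feasibility tie policy use to confirmed effectiveness of the programme as a whole, which the randomised comparison tests.

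**A time-ordered replacement model is not clearly better.** Relating months 0–3 engagement to month 3–6 weight change needs engagement split at month 3, which the article does not show to be available. If it also adjusts for change to month 3, it excludes benefit already gained by then and so answers a different question. It still leaves unmeasured motivation. This objection stands, so such a model is at most an optional addition.

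**Conclusion.** The concern holds in a limited form. The article plans to estimate the impact of self-selected, post-randomisation engagement on weight loss over the same period, and names only sociodemographic characteristics as other terms. As written, the model cannot distinguish an effect of engagement from readiness or from reverse causation.

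How far this would mislead is unknown. Under the assumed correlations, the false-positive rate from confounding runs from nominal to about 70%, and from reverse causation from about 11% to 81%. These ranges rest on no true logging effect, 97 completers, SD 3.7 kg and sociodemographics unrelated to motivation.

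The point is minor. It concerns a supporting within-arm analysis; the randomised primary comparison and the sample size are untouched.

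**What to change.** 1. Add baseline stage of change and baseline weight to the within-arm model. Both are collected under Table 2 and Data Collection Methods. This reduces confounding by readiness as far as stage captures it; it does not deal with reverse causation.
2. Replace *impact* with *association*, in the analysis plan and when reporting.
3. State that the analysis is exploratory and does not identify the effects of individual components, and state the time windows for engagement and weight loss.
4. Optionally, if engagement records are dated, add a sensitivity analysis of months 0–3 engagement against month 3–6 weight change, alongside the planned model and not in its place. Its outcome window is shorter and it answers a different question.

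The cost is a wording change, two more model variables (stage, if entered as categories, uses several coefficients) and a more modest conclusion. No new visit, measurement or participant is needed for items 1 to 3.
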